Random assignment. Randomization of the CBO-recruited sample (n=300) into RIWP or treatment-as-usual waitlist control group (TAU) will occur after completion of timepoint 1 surveys and will be based upon a computerized algorithm that stratifies randomization by CBO site.

RIWP implementation. RIWP will be implemented with 30 participants from each CBO site (n=150) from Months 5-12. RIWP will be integrated into existing activities and services in different ways at each site, with the goal of creating a sustainable intervention and multilevel change. All RWIP activities (Learning Circles and advocacy) will be conducted remotely for now. Once state and UNM COVID restrictions are lifted, some in-person Learning Circles and advocacy meetings may occur. The treatment-as-usual waitlist control group will participate in RIWP after two years (3 timepoints) of data collection, from Months 29-35. RIWP involves a sustainable and replicable partnership model between refugees, CBOs, and universities (see Figure 1 for conceptual model). Newcomer families and undergraduate advocates work together for 16 weeks to: a) increase newcomers’ abilities to navigate their new communities; b) improve newcomers' access to community resources; c) enhance meaningful social roles by valuing newcomers' cultures, experiences, and knowledge; d) reduce newcomers' social isolation; and e) increase community responsiveness to newcomers. RIWP is implemented by university students enrolled in a 2-semester course, and has two elements: 1) Learning Circles, which involve cultural exchange and one-on-one learning opportunities; and 2) Advocacy, which involve collaborative efforts to mobilize community resources related to health, housing, employment, education, and legal issues and to create policy/system changes. Meeting in weekly Learning Circles, newcomers and their student partners learn from each other during cultural exchange time designed to facilitate sharing of cultural and intergenerational knowledge and to help newcomers recognize their contributions and potential to effect changes in their communities. During one-on-one learning time, newcomer and student participants practice English, fill out job applications, and engage in other activities newcomers want to pursue to expand knowledge, improve skills, or accomplish goals. RIWP is holistic, multilevel, and strengths-based, and has an explicit social justice orientation that is informed by an ecological perspective. A holistic intervention is essential because it addresses the multiple sources of newcomers’ psychological distress, including psychological (past traumas), material (poverty, lack of access to resources), physical (physical ailments from war, violence and deprivation), social (loss of meaningful social roles and social support), educational (limited English proficiency, literacy), and cultural disconnection from traditional cultural practices). A strengths-based perspective is important because newcomers have survived in the face of tremendous hardships and have numerous strengths on which to build, including cultural knowledge (and often extensive cross-cultural experience), resourcefulness (experience operating in resource scarce situations), effective coping strategies (that have enabled them to survive), multilingual abilities (many arrive already speaking two or more languages), and often strong family and community bonds and support. Newcomers are often pathologized by well-intentioned service providers and systems, rather than recognizing that most are resilient people who have faced abnormally difficult circumstances. Not only is it crucial for newcomers’ mental health and well-being to acknowledge their expertise and build upon their strengths, but also their knowledge and experiences are assets from which other Americans can benefit. Thus, mutual learning is an intentional and core component of RIWP. This emphasis also ensures that RIWP is appropriate for multiple linguistic and cultural groups who can participate simultaneously and learn from one another as well as from longer-term residents of the U.S. Guided by ecological theory, RIWP focuses not only on newcomers adjusting to their new contexts, but also on changing environments when they are inequitable or constraining (e.g., mobilization or redistribution of resources). Ensuring that RIWP creates change at multiple levels is important because newcomers have urgent learning, resource, and health needs that must be addressed at the individual level in order to enable them to work collectively with others to create community and structural changes that address the root causes of mental health disparities and social inequities, which result in sustainable social change.

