**Aim 1.** Test the effects of the RIWP intervention to reduce adverse consequences of the COVID-19 pandemic. The principal objective of this study is to test the efficacy of the RIWP intervention for participants recruited from CBOs. Because only individuals recruited from the CBO sample are eligible to be randomized to receive the RIWP intervention or treatment as usual, analysis for this aim includes only CBO participants. To examine the effects of the RIWP intervention, we propose a linear model with random effects for individuals. As randomization happens within CBO, there is not an explicit random effect for this included, but we do propose to use sandwich estimators,^99,100^ to adjust standard errors for any unexpected impacts of this clustering. In mixed notation the model for psychological distress is:

${Distress}_{ti}= B_{00}+{B_{01}\left( RIWP \right){+B}_{02}\left( Time \right){+B}_{03}\left( Time*RIWP \right){+\boldsymbol{B}}_{\mathbf{0}\boldsymbol{N}}\left( \boldsymbol{covariates} \right)+ r_{0ij}+r_{2ij}(Time)+ e}_{ij}$

where participation in the RIWP plus CBO is indicated by a dummy code for RIWP. Because baseline data is collected before randomization, time is centered at baseline and our aim is answered by B_03_ which is the difference in slopes of levels of distress, adjusted for covariates, between those who experience RWIP+CBO intervention and those in the CBO group.

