**Aim 2**. Test the effects of engagement with CBOs to reduce adverse consequences of the COVID-19 pandemic. Analyses will use both the CBO sample and the random sample of Latinx respondents from across the state. The primary predictor is whether the participant is recruited through the CBO or random community sample. Our analyses test whether respondents recruited from CBOs differ from those in the random sample in outcomes and whether those differences change over time. While the comparison sample is a random probability sample of Latinx immigrants, the CBO sample consists of respondents already connected to a CBO, thus we propose to use propensity score matching^101,102^ with data collected at baseline to match those in each sample. The matched samples used for data analysis will adjust for systematic differences between the random sample and those who engage with CBOs. Our baseline measures have been chosen to include variables which are likely to predict an individual’s exposure to a CBO. To examine the effects of engagement with CBOs, we propose a longitudinal model with random effects for both individuals and CBOs. The model will also adjust for effects of the RIWP intervention observed in Aim 1. We note that the adjustment for clustering within CBOs only takes place for those in the CBO arm; in the comparison arm where there is no nesting, these random effects are assumed to be zero.^103,104^ In mixed notation the model for psychological distress is:

${Distress}_{tij}= B_{000}+{\gamma_{001}\left( CBO \right)+{B_{100}\left( Time \right)+\gamma_{101}\left( CBO*Time \right)\boldsymbol{+B}}_{\boldsymbol{010}}\left( \boldsymbol{covariates} \right)+{B_{020}\left( RIWP \right)+B_{030}\left( RIWP*Time \right)+ u_{00j}+u}_{10j}\left( Time \right)+r_{0ij}+r_{1ij}(Time)+ e}_{tij}$

where CBO is an indicator indicating whether individual *i* is engaged with the CBO, Time is a variable indicating the time of observation in years. For this analysis, Time will be centered around the midpoint of the study because engagement with the CBO is ongoing from before the study began. Thus, our aim is answered by Y_001_ which is the difference in mean levels of distress, adjusted for covariates, between those who experience the CBO and those in the random sample and by Y_101_ which is the difference in slopes over time between those who experience the CBO and those in the random sample.

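### Aim 1 calls the slope contrast B_03 covariate-adjusted, but the printed model enters covariates only as main effects, which do not adjust a slope for time-invariant covariates

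*Protocol*

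**What the plan says.** All of this stands in the Protocol, Data Analysis/Statistical Considerations, unless noted.

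- **Aim 1, estimand.** Time is centered at baseline, and B_03, the coefficient on Time by RIWP, answers the aim. It is described as "the difference in slopes of levels of distress, adjusted for covariates, between those who experience RWIP+CBO intervention and those in the CBO group".
- **Aim 1, model.** The fixed part is an intercept, RIWP, Time, Time by RIWP, and one term B_0N for covariates. The random part is an intercept and a Time slope per person. There is no covariate-by-Time product.
- **Aim 1, allocation** (Data Collection Procedures, random assignment). Randomization "will be based upon a computerized algorithm that stratifies randomization by CBO site".
- **Aim 2, model.** It has the same structure, with one covariate term B_010 and no covariate-by-Time product. RIWP terms and CBO random effects are added.
- **Aim 2, estimands.** The level contrast gamma_001 is "the difference in mean levels of distress, adjusted for covariates, between those who experience the CBO and those in the random sample". The slope contrast gamma_101 is "the difference in slopes over time between those who experience the CBO and those in the random sample", with no mention of covariates.
- **Aim 2, matching.** Propensity scores from baseline data come first: "The matched samples used for data analysis will adjust for systematic differences between the random sample and those who engage with CBOs".
- **Status of the time form.** Intercept plus linear change is a working assumption. The final form is to be chosen in the random comparison sample, with linear change, piecewise change and adjustment for time-varying events named as candidates.

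**The concern.** In a growth model, a person-level covariate needs a product with Time to act on the slope. Its main effect explains only differences in level. The Aim 1 sentence therefore credits B_03 with a property that the equation above it does not give for time-invariant covariates such as sex assigned at birth, birthplace or race/ethnicity, all of which the survey collects.

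Two things are at stake. In Aim 1, covariates that predict change do nothing to sharpen the coefficient that answers the study's principal objective, and a chance imbalance in them goes uncorrected. In Aim 2, which is not randomized, one of the two deciding coefficients depends on matching alone. If balance is imperfect, or erodes because the groups drop out at different rates, the covariate term does not help the slope.

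**Working it through.** **The plan's own figure.** The only figure nearby is the Aim 1 power of .91. Inputs from the Power paragraph: 150 per arm less 10% attrition = 135, effect size 0.3, baseline-posttest correlation .68. Two-sided 5% is assumed, since no alpha is stated. Residual SD = sqrt(1 - 0.68^2) = 0.733. SE = 0.733 x sqrt(2/135) = 0.0892. 0.3/0.0892 = 3.36, and power = 0.919. The figure is reproduced. It comes from a pre/post calculation that does not involve the covariate term, so this point leaves it unchanged.

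**Step 1: why a main effect cannot reach the slope.** With complete data on a common schedule, the mixed model is equivalent to a joint regression of each person's least-squares intercept and slope. The printed model puts RIWP and the covariates in the intercept equation, but only RIWP in the slope equation. When the regressors of one equation are a subset of those of the other, the joint estimate for the smaller equation is its ordinary least-squares estimate. So B_03 is the plain difference in mean slopes, whatever covariates enter as main effects.

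**Step 2: numerical check.** The model was fitted to simulated data with five waves 8 months apart and one time-invariant covariate X. The Aim 2 version omitted the RIWP terms and CBO random effects. The table shows how far the slope contrast moves when X is added as a main effect.

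| Setting | Largest change in slope contrast |
|---|---|
| Aim 1, complete data | 3e-16 |
| Aim 2, complete data | 5e-16 |
| Aim 1, 10% dropout | 0.003 and 0.007 in two sets of runs |
| Aim 2, nominal 30% dropout depending on X | 0.007 |

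The result is exact with complete data and nearly so with dropout.

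**Step 3: Aim 1 precision.** Assumptions, not from the protocol: slope variance 0.03, residual variance 0.35, and X with SD 1 that changes the slope by b SD/year. The wave times are 0 to 32 months in steps of 8/12 year, so the sum of squared deviations is (8/12)^2 x 10 = 4.444. The variance of a person's estimated slope given X is 0.03 + 0.35/4.444 = 0.1087. Without the interaction, b^2 is added. SE of B_03 = sqrt(2 x variance/150).

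| b | Variance without X by Time | SE without | SE with | Reduction |
|---|---|---|---|---|
| 0.05 | 0.1112 | 0.0385 | 0.0381 | 1% |
| 0.10 | 0.1188 | 0.0398 | 0.0381 | 4% |
| 0.15 | 0.1312 | 0.0418 | 0.0381 | 9% |

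Fitted models at b = 0.10 gave 0.0399 and 0.0380, about 5%. At that value the gain is worth 0.1188/0.1087 = 1.09, or about 9% more participants.

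**Step 4: Aim 2 slope bias.** Expected bias in gamma_101 is approximately the imbalance in X times b. Over 32 months, multiply by 32/12 = 2.67.

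- 0.1 SD x 0.10 = 0.01 SD/year, or 0.027 SD over 32 months.
- 0.3 SD x 0.10 = 0.03 SD/year, or 0.08 SD over 32 months.

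A simulation at 0.3 SD (150 against 400 people, 10% and 30% dropout, 25 trials) gave mean slope contrasts of 0.0364 with no covariate, 0.0358 with the main effect and 0.0100 with X by Time. Simulation error is about sqrt(0.1188 x (1/150 + 1/400))/sqrt(25) = 0.007. The first two values therefore agree with 0.03, and the last agrees with zero.

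A second check used a larger, unmatched imbalance (0.5 SD) and b = 0.15, so the expected bias is 0.075/year. It gave 0.072 with or without the main effect and -0.006 with X by Time. With X balanced, as matching intends, the main-effect model gave -0.004 (SE 0.005).

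**The case against.** Several parts of the case on the other side stand and limit the point.

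- **Aim 1 is not biased.** A reader might infer that B_03 is invalid. Allocation is random within CBO site, so B_03 is unbiased with no covariates at all. Leaving out covariate-by-Time terms in a randomized growth model is an ordinary choice. What is wrong is describing the result as adjusted.
- **Aim 2 makes no false statement.** A reader might infer that the protocol claims covariate adjustment for both slopes. In Aim 2 it attaches that wording only to the level contrast, which a main effect does adjust.
- **gamma_101 is not without protection.** Matching on baseline variables balances them for level and slope alike, and the balanced check above shows no bias. The gap concerns only imbalance that matching leaves or attrition creates.
- **Time-varying covariates.** Entered as main effects, these can adjust a slope. The protocol names unemployment and COVID infections as candidates, and surveys are repeated five times. The point is therefore confined to time-invariant covariates.
- **The equations are provisional, and details may sit in an SAP.** This is true of the covariate list. But the alternatives left open are time forms and time-varying events, and none is a baseline covariate-by-Time term. A piecewise form would carry the same gap forward. The B_03 sentence is also a statement in the current text, not a detail deferred.
- **The sizes are assumed.** No imbalance or covariate-slope effect comes from the protocol, and the 25-trial simulation is noisy. The algebra does not depend on either.

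**Conclusion.** The definition of B_03 claims an adjustment that the printed Aim 1 model does not deliver for time-invariant covariates. That conclusion is exact for complete data and holds within about 0.007 in the dropout simulations.

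The consequence is modest. In Aim 1 it is a loss of about 1-9% in the standard error for slope effects of 0.05-0.15 SD/year, under the assumed variances, plus no correction for chance imbalance. In Aim 2 the wording is not wrong and matching is the main safeguard. The covariate term simply adds nothing for the slope if balance is imperfect, with a bias of about 0.01-0.03 SD/year for an assumed 0.1-0.3 SD remaining imbalance and a 0.10 SD/year slope effect. The protocol's own attrition assumptions, 10% in the CBO sample and 30% in the random sample, make some loss of balance possible but do not show that it will occur. No figure in the protocol changes.

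**What to change.** In both equations, add Time interactions for a short prespecified list of baseline covariates, keeping their main effects. In Aim 1 include CBO site by Time, since site stratified the randomization. State that if another time form replaces linear change, the same covariates will be interacted with that form.

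The cost is a change to two equations and a few degrees of freedom: five sites need four site-by-Time terms, plus one for each single-parameter covariate, with 300 participants in Aim 1. No new data are needed.

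If the interactions are not wanted, delete the words 'adjusted for covariates' from the definition of B_03. That makes the text accurate but gives up the precision in Aim 1 and the second safeguard in Aim 2.

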
# OBJECTIVES/AIMS

The goal of this research is to advance the science of multilevel mental health interventions that aim to reduce the disparate, adverse mental health, behavioral, and socioeconomic consequences of the COVID-19 pandemic that are a result of complex interactions between underlying structural inequities and numerous barriers to health care. This community-based participatory research study builds on a long-standing collaboration with 5 community-based organizations (CBOs) and employs a longitudinal waitlist control group design with 5 time points over 32 months. A random probability sample of 1000 Latinx immigrants (RS) will be compared with 240 Latinx immigrants and 60 African refugees recruited through CBOs and randomly assigned to an efficacious peer advocacy and learning model (RIWP; n=150) or a treatment-as-usual waitlist control group (TAU; n=150). This innovative design allows for testing of three nested levels of intervention: 1) peer intervention model; 2) engagement with CBOs; and 3) structural interventions expected in response to the pandemic (e.g., state relief for mixed status families and expanded health insurance coverage), to which all 1300 participants would potentially be exposed. We propose three primary aims to advance mental health intervention and disparities research:

**Aim 1.** Test the effects of the RIWP intervention to reduce adverse consequences of the COVID-19 pandemic for Latinx and Black immigrants and refugees.

**1.1** *Primary Outcomes:* RIWP participants will have decreased psychological distress, daily stressors, and economic precarity as compared to randomly assigned treatment-as-usual waitlist control group (TAU).

**1.2** *Secondary Outcomes:* RIWP participants will have increased protective factors (social support, access to resources, English proficiency, cultural connectedness, health services use).

**Aim 2.** Test the effects of engagement with CBOs to reduce adverse consequences of the COVID-19 pandemic for Latinx and Black immigrants and refugees.

**2.1** *Primary Outcomes:* CBO participants will have decreased psychological distress, daily stressors, and economic precarity as compared to the comparison group of randomly sampled immigrants (RS).

**2.2** *Secondary Outcomes:* CBO participants will have increased protective factors (social support, access to resources, English proficiency, cultural connectedness, health services use).

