## *Data Analysis/**Statistical Considerations*

Quantitative data analysis. This longitudinal study design will use random effects (multilevel) models, which account for both repeated measures of individuals and the fact that in one arm individuals are clustered within CBOs. These models allow for outcomes to be missing under the MAR assumption (data is missing at random conditional on the observed outcomes and covariates),^89–91^ which we expect will be adequate. If there is a substantial amount of missing data for covariates or evidence that a more inclusive imputation model should be used, then we will use multilevel multiple imputation implemented via MITML package.^92^ Model assumptions will be evaluated using the comparison group for each analysis, and any modification to the analyses to address violations will be made before final analyses using only comparison group data.

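### The Aim 2 model gives the CBO and random samples common person-level and residual variances, the planned check cannot test this, and the CBO test can be mis-sized if the variances differ

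*Protocol*

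**What the plan says.** All references are to the protocol, Data Analysis/Statistical Considerations, unless another section is named.

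- **Aim 2 paragraph, model.** The text reads: "we propose a longitudinal model with random effects for both individuals and CBOs". The equation has CBO effects on intercept and slope (u₀₀ⱼ, u₁₀ⱼ), person effects on intercept and slope (r₀ᵢⱼ, r₁ᵢⱼ) and a residual (e_tij). The one stated difference between samples concerns the CBO effects: "in the comparison arm where there is no nesting, these random effects are assumed to be zero". The person and residual terms carry no index for sample.
- **Aim 2 paragraph, other features.** The samples are matched first ("thus we propose to use propensity score matching"), with no ratio given. The model also has RIWP terms: "The model will also adjust for effects of the RIWP intervention observed in Aim 1".
- **Opening paragraph, checks.** "Model assumptions will be evaluated using the comparison group for each analysis". On repairs: "any modification to the analyses to address violations will be made before final analyses using only comparison group data". Objectives/Aims names the random sample as the Aim 2 comparison group.
- **Robust standard errors.** Sandwich estimators are named for Aim 1 and for the mediation models, but not for Aim 2.

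**The concern.** Aim 2 is not randomized, and nothing in the design makes the two variances equal. One sample is a statewide draw from household lists. The other is recruited through five organizations and includes 60 African refugees. Exclusion for severe mental illness applies to the CBO sample only (Target Population and Inclusion/Exclusion Criteria). These features could push the CBO variance either up or down.

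Ordinarily an analyst would compare the variances and adapt the model. The checking rule prevents that, because data from one sample cannot show a difference between two. At stake is the standard error of γ₀₀₁, one of the two coefficients that answer Aim 2. With a pooled variance it is too small if CBO members vary more and too large if they vary less. The distortion grows when the comparators, who dominate the pooled estimate, greatly outnumber the CBO members.

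**Working it through.** **Inputs from the protocol.** Five CBOs and 300 CBO participants, half RIWP and half TAU. With 10% attrition, 270 remain: 54 per CBO (27 TAU, 27 RIWP), so 135 TAU. The random sample of 1000 (formerly 300) with 30% attrition leaves 700 (formerly 210). The Power paragraph gives ICC .03, baseline-posttest correlation .68 and effect size .30.

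**Assumptions, because the protocol gives no figure.** Two-sided 5% level. CBO-to-random-sample variance ratio from .5 to 2. Comparators kept after matching: 270 (1:1) or 700 (all completers, the ceiling).

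**Step 1: the plan's own figure.** The stated Aim 2 power is .92. Residual variance is 1 − .68² = .5376, and SE² = .5376 × (.03/5 + 1/270 + 1/n).
- n = 210: SE² = .5376 × .01447 = .00778, SE = .0882, power = Φ(.30/.0882 − 1.96) = .925.
- n = 700: SE² = .5376 × .01113 = .00598, SE = .0774, power = .972.

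The stated figure reproduces with the former random sample of 300. This checks the inputs only. The protocol reports no type I error figure for Aim 2.

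**Step 2: which contrast γ₀₀₁ is.** With RIWP terms in the model, γ₀₀₁ compares TAU with the random sample. Its true variance is τ²/5 + σ²_C/135 + σ²_R/n, where τ² is the CBO variance and σ²_C and σ²_R are the within-sample variances. The common-variance model replaces both of the latter by one pooled estimate.

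**Step 3: mechanism, with no CBO term.** Set σ²_R = 1. The pooled variance is p = (n + 270 × ratio)/(n + 270). Size is 2[1 − Φ(1.96 × √(A/B))], with A = p(1/135 + 1/n) and B = ratio/135 + 1/n.
- n = 700, ratio 2: p = 1.278, A = .01130, B = .01624, size 10.2%.
- n = 700, ratio .5: p = .861, A = .00761, B = .00513, size 1.7%.
- n = 270, ratio 2: p = 1.5, A = .01667, B = .01852, size 6.3%.
- n = 270, ratio .5: p = .75, A = .00833, B = .00741, size 3.8%.

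These bound the problem. They are not the plan's model, which has a CBO random intercept in the CBO sample only. That intercept absorbs part of the mismatch.

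**Step 4: the plan's model.** Simulation with no true effect, REML-type estimation for five CBOs of 54, and 400,000 replicates per setting. τ² is .03 times the random-sample variance. Entries are size in %, with a 1.96 cutoff and then with a Satterthwaite-type t.

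| Comparators | Ratio | Common variance | Separate variances |
|---|---|---|---|
| 700 | .5 | 5.7 / 4.3 | 7.9 / 5.6 |
| 700 | 1 | 7.0 / 5.2 | 7.0 / 5.2 |
| 700 | 2 | 8.6 / 6.3 | 6.0 / 4.7 |
| 270 | .5 | 6.6 / 5.1 | 6.8 / 5.3 |
| 270 | 1 | 6.4 / 5.1 | 6.4 / 5.1 |
| 270 | 2 | 6.3 / 5.0 | 5.8 / 4.7 |

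A second set (200,000 replicates) holds the ICC at .03 within the CBO sample, so τ² scales with the CBO variance. With 700 comparators and ratios .5 to 2:
- common variance: 4.0-9.3% (1.96) or 3.3-6.4% (t);
- separate variances: 6.6-7.1% (1.96) or 5.0-5.2% (t).

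At 1:1 matching the two approaches differ by about half a point or less.

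**Step 5: two sources of error.** With equal variances and 700 comparators, the 1.96 test already has size 7.0%. That excess comes from having five CBOs, and the t reference removes most of it (5.2%). Only the departure from 7.0% (or 5.2%) as the ratio moves is due to unequal variance.

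**The case against.** The strongest reply has five parts.

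- **The equation is provisional.** The protocol calls it a relatively simple working model, and covariance detail is commonly left to an SAP. This stands in part. But the alternatives the protocol lists concern the shape of change over time and time-varying events, not variances by sample, and that exploration also uses the random sample only. The checking rule itself is fixed here.
- **Matching may remove the problem.** This stands: at 1:1 the effect is negligible. The ratio is not stated, so neither 270 nor 700 can be assumed.
- **Separate variances alone can make matters worse.** This stands. With a 1.96 cutoff and a ratio of .5, size goes from 5.7% to 7.9%, because the conservative pooled variance had hidden the five-CBO excess. The remedy therefore needs a small-sample reference as well.
- **The Aim 1 check would look at TAU data.** Aim 1 includes CBO participants only, so its comparison group is TAU, and an analyst could set its variance beside that of the random sample. But nothing makes this part of the Aim 2 check, which as written uses random-sample data.
- **The rule is a deliberate guard** against modelling choices driven by treated-arm outcomes. It is, and it is worth keeping.

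A reader might infer that the Aim 2 test is mis-sized as planned. The documents do not support that. They give no variances by sample, no direction for any difference and no matching ratio. Nor does the sentence about zero random effects assert equal variances: it concerns CBO effects, and the common variances follow from the unindexed terms in the equation.

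**Conclusion.** The point holds as a conditional weakness and a cheap improvement. The Aim 2 model as written has common person-level and residual variances, and its comparison-group-only check cannot show whether they are equal. At ICC .03, with 700 comparators and an assumed ratio of .5 to 2, the size of the γ₀₀₁ test runs over about 3-6% with a t reference or 4-9% with 1.96, against about 5% and 7% with equal variances.

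This rests on three assumptions: variances that still differ after matching and covariate adjustment, many more comparators than CBO members kept, and a two-sided 5% level. The slope coefficient γ₁₀₁, which also answers Aim 2, was not simulated, so nothing is claimed about its size.

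**What to change.** 1. In the Aim 2 paragraph, specify separate person-level and residual variances for the CBO and random samples for the continuous outcomes. Pair this with a small-sample degrees-of-freedom reference, such as Satterthwaite or Kenward-Roger, because there are only five CBOs.
2. In the opening paragraph of the analysis section, state that equal variance between samples is not assumed. No data-driven comparison is then needed, and the guard against outcome-driven modelling stays intact.

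With both parts in place, simulated size was 4.7-5.6% over the ratios and matched sizes tried at ICC .03. The cost is a few extra variance parameters and slightly wider intervals from the t reference. No new data are needed.
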